### Test drugs

2.10

Test drugs are Modified Shenling Baizhu Powder and Modified Shenling Baizhu Powder mimetic agent (placebo), provided by the Department of Pharmacy, Hospital of Chengdu University of TCM (Sichuan, China). Whole ingredients of Modified Shenling Baizhu Powder are LABLAB SEMEN ALBUM (Bai bian dou)100 g,ATRACTYLODIS MACROCEPHALAE RHIZOMA (Bai zhu100 g, PORIA(Fuling)100 g, PLATYCODONIS RADIX (Jie geng)150 g, NELUMBINIS SEMEN(Lian zi),50 g, CODONOPSIS PILOSULA (Dang shen)100 g, AMOMI FRUCTUS(Sha ren) 50 g, DIOSCOREAE RHIZOMA (Shan yao) 100 g, COICIS SEMEN (Yiyiren) 200 g, GLYCYRRHIZAE RADIX ET RHIZOMA (Gan cao) 100 g, Ephedrae Herba (Ma huang) 50 g, ARMENIACAE SEMEN AMARUM (Ku xing ren) 75 g. One dose every 5 days, 10 g each time, 3 times a day.

The prescription herbs are mixed, processed, filtrated, and pressure spray dried to produce granules, which are packaged into single-dose sachets, each weighing 10 g. Placebos are composed of starch with no active ingredients. By the addition of various food colorings, placebos are made to look and taste as close to real particles as possible.

## Interventions

3

### Treatment plan

3.1

Standards Western medicine will be used for both groups. According to GOLD^[4]^ and the Guidelines for the Diagnosis and Treatment of Chronic Obstructive Pulmonary Disease (Revised 2013),^[13]^ participants will receive inhalation treatment with tiotropium bromide powder (Si Li Hua, Boehringer Ingelheim Pharma GmbH & amp; Co. KG [Germany], 18 μg×30 capsules), 18 μg per inhalation, once a day. Also, the proper use of inhalants will be taught to all participants, who would also have to stop smoking and prevent colds. Throughout the study, patients are not allowed to receive other COPD-related medications or herbal treatments except in emergencies.

Experimental group: Participants will take 10 g Modified Shenling Baizhu Powder 3 times daily, dissolved in 100 mL of warm water, for 6 months.

Control group: participants will receive 10 g placebo granules 3 times daily, dissolved in 100 mL of warm water, for 6 months. The measurements will be in accordance with the experimental group.

### Outcome measures

3.2

Primary outcome: FEV1 after bronchodilator use at 1, 3, 6, 9, 12, 15, 18 months

Secondary outcomes: at 1, 3, 6, 9, 12, 15, 18 months

1.the declines, the between-group difference in the change from baseline to 18 months in FEV1 before bronchodilator use, FVC, FEV1/FVC, FEV1%pred after bronchodilator use;2.the changes in mMRC score, CAT score, SGRQ score;3.Frequency, interval, duration, and severity of COPD exacerbations; time to first COPD exacerbation; and the use and cost-benefit analysis of rescue medications; smoking status; safety assessment.

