**Methods::**

The study is a prospective, randomized, placebo-controlled, double-blind trial in which 270 eligible participants will be randomly assigned to either the experimental or control group in a 1:1 ratio. Both groups will receive the standard Western medication. Meanwhile, participants in the experimental group will undergo Modified Shenling Baizhu Powder, while those in the control group will undergo a matched placebo. The course of treatment is 6 months with 12 months of follow-up. Primary outcome is the forced expiratory volume in 1 second (FEV1) after bronchodi-lator use. The secondary outcomes include the declines and the between-group difference in the change from baseline to 18 months in FEV1 before bronchodilator use; the forced vital capacity (FVC), FEV1/FVC, FEV1%pred after bronchodilator use, modified British medical research council, COPD Assessment Test, St George's Respiratory Questionnaire (SGRQ); frequency, interval, duration and severity of COPD exacerbations; time to first COPD exacerbation; administration of rescue medication and a cost-effectiveness analysis; Smoking status. A safety assessment will also be performed during the trial.

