### Sample size

2.4

The sample size was calculated on the primary outcome (the forced expiratory volume in 1 second (FEV1) at 18 months). According to the previous literature,^[10]^**t**he mean value of FEV1 in the control group is estimated to be 2.54 with a standard deviation of 0.65. After the herbal treatment the mean value of FEV1 in the experimental group is 2.83 with a standard deviation of 0.73. The calculation of the sample size for the experimental and control groups of each was 121 cases using the software Power Analysis and Sample Size version 11.0 (PASS 11.0). Altogether, 268 participants are recruited at a 10% dropout rate. For the actual study, 135 cases per group will be included.

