### Statistical analysis

3.7

The intention to treat principle will be followed for all data analysis. The Statistical Package for the Social Sciences version 22.0 (SPSS 22.0, Chicago, IL) will be used to analyze the data. The analysis method should be based on the characteristics of the data distribution: The measurement data will be expressed as mean ± standard deviation and normal distribution, paired *t* test will be used for comparison before and after treatment, *t* test will be used for between-group comparisons (homogeneity test of variance will be performed with 0.05 as the test standard), and rank sum test will be used for comparison between groups. Chi-square test will be used for enumeration data, and rank-sum test will be used for grading data. Bilateral tests will be used for all tests, with *P* < .05 indicating a significant difference. For baseline data, the full analysis set (FAS, including completed cases and dropout cases, excluding censored cases) is used, and the full analysis set and the per-protocol set(PP set, including completed cases, excluding dropout cases and censored cases) are used for efficacy evaluation, which can enhance the reliability of trial results when the conclusions of the two analyses are consistent. When inconsistencies arise, differences should be fully discussed and explained. In the analysis of the full analysis set, the missing data are substituted by the method of sequence mean value.

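### Section 3.2 makes post-bronchodilator FEV1 at seven visits the primary outcome, section 2.4 makes it FEV1 at 18 months, and nothing says which visit decides the trial

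*Protocol article*

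**What the plan says.** Four places in the protocol article bear on the primary outcome.

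- **Section 3.2, Outcome measures:** "Primary outcome: FEV1 after bronchodilator use at 1, 3, 6, 9, 12, 15, 18 months". No visit is singled out.
- **Section 2.4, Sample size:** "The sample size was calculated on the primary outcome (the forced expiratory volume in 1 second (FEV1) at 18 months". One visit is named, and one pair of means is used for the calculation.
- **Abstract, Methods:** "Primary outcome is the forced expiratory volume in 1 second (FEV1) after" bronchodilator use. No time point is attached.
- **Section 3.7, Statistical analysis:** for normally distributed measurements a t "test will be used for between-group comparisons", with a rank sum test as the other option. "Bilateral tests will be used for all tests", with P "< .05 indicating a significant difference". No deciding visit is named.

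Sections 2.1 and 3.1 set 6 months of treatment, and section 2.1 adds 12 months of follow-up. Months 1, 3 and 6 are therefore within the treatment period, and months 9, 12, 15 and 18 come after it.

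**The concern.** The confirmatory hypothesis is stated in two ways that do not agree. Under section 2.4 it is one comparison at 18 months. Under section 3.2 taken alone, a difference at any listed visit could be presented as a result on the primary outcome.

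The choice matters scientifically as well as for error control. A difference at month 3 would show an effect during treatment. A difference at month 18 would show that something persists a year after treatment ends. The Discussion describes the aim as slowing the deterioration of lung function, which an early on-treatment difference would not by itself demonstrate.

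What is at stake is whether the deciding comparison is fixed before unblinding. If the visit can be picked from seven after the results are known, the 5% threshold no longer describes the chance of a false claim on the primary outcome.

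**Working it through.** **Step 1. Does the sample size correspond to a single test?**

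Inputs from section 2.4: control mean 2.54 (SD 0.65), experimental mean 2.83 (SD 0.73), 121 per group. Two-sided 5% comes from section 3.7. Power is not stated.

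Difference = 2.83 − 2.54 = 0.29. Pooled SD = √[(0.65² + 0.73²)/2] = √[(0.4225 + 0.5329)/2] = 0.691.

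n per group = (z₀.₉₇₅ + z_power)² × (0.65² + 0.73²) / 0.29²

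At 90% power: (1.960 + 1.282)² × 0.9554 / 0.0841 = 10.51 × 11.36 ≈ 119.4, so 120. The exact two-sample t test gives power 0.899 at 120 and 0.902 at 121, so 121 is the first size above 90%. Two-sided powers of 80%, 85% and 95% would give 90, 102 and 148. The stated 121 is thus reproduced as **one** two-sided 5% test at an inferred power of 90%. Dropout: 121/0.9 = 134.4, so 135 per group, which matches the plan.

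**Step 2. Type I error if 18 months alone decides.** One test at 0.05 gives 5%.

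**Step 3. Type I error if any visit could decide.** This needs two assumptions that the documents do not supply: a rule that significance at any one of the seven visits is success, and a correlation between visits.

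Independent visits: 1 − 0.95⁷ = 0.302.

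Equal correlation r: write each visit's test statistic as √r·U + √(1−r)·e, with U and e independent standard normals. With c = 1.96,

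P(any |Z| > c) = 1 − ∫ φ(u) [Φ((c − √r·u)/√(1−r)) − Φ((−c − √r·u)/√(1−r))]⁷ du.

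| Assumed r | P(at least one of seven significant) | Multiple of 5% |
|---|---|---|
| 0 | 30.2% | 6.0 |
| 0.6 | 20.5% | 4.1 |
| 0.8 | 14.9% | 3.0 |
| 0.9 | 11.4% | 2.3 |
| 0.95 | 9.2% | 1.8 |
| 0.99 | 6.7% | 1.3 |

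If correlation instead decays with time between visits (simulated at the protocol's visit months), the figures are 18.9%, 14.4% and 11.3% for correlations of 0.8, 0.9 and 0.95 per 3 months.

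**Step 4. What it would cost to keep seven primaries with error control.** With Bonferroni, each test is at 0.05/7 = 0.00714. At 121 per group, power for any one visit falls to about 72%, taking the same 0.29 difference. For 90%: (2.690 + 1.282)² × 11.36 ≈ 179.2, so 180 per group before dropout.

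**The case against.** The strongest reply is that section 2.4 does name a single primary and the arithmetic bears it out: 121 per group is the answer for one test. On that reading the type I error is 5% and nothing is inflated. This stands as far as it goes. It would be too strong to say that the trial has no primary hypothesis.

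A second reply is that the visit list in section 3.2 is only an assessment schedule. The same seven months introduce the secondary outcomes, among them a change from baseline to 18 months, time to first exacerbation and a cost-benefit analysis of rescue medication. These cannot be seven separate visit-specific endpoints. That is a plausible reading of the primary line too. But the line is labelled as the primary outcome, no visit in it is marked as decisive, and nothing says that section 2.4 prevails.

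A third reply is that multiplicity rules and longitudinal models are commonly left to an analysis plan. That is fair, and their absence from this article is not the point. The point is that two sections of the same document fix the primary time point differently.

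A reader might go further and infer that the false-positive rate on the primary is two to four times 5%. The documents do not support this as a fact. They never say that FEV1 is tested for success at each visit or that a win at any visit suffices, and they give no between-visit correlation. Even under an any-visit rule, two to four times holds only for equal correlations of about 0.6 to 0.93.

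**Conclusion.** The contradiction is real and concerns the confirmatory hypothesis: seven visits in section 3.2, one in section 2.4, none in the abstract, and no deciding visit in section 3.7. It should be resolved before unblinding, because a choice made afterwards would not be credible.

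The effect on type I error is conditional. It is nil if 18 months alone decides. Under an assumed any-visit rule it runs from just above 5%, when visits are almost perfectly correlated, to 30% when they are independent. The main uncertainty is which reading the sponsor intends. The between-visit correlation matters only if the any-visit reading applies. The reproduction of 121 per group rests on an inferred power of 90%.

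**What to change.** State in the abstract and in sections 2.4 and 3.2 that the single primary outcome is the between-group difference in post-bronchodilator FEV1 at 18 months, which is the visit the sample size uses. List months 1 to 15 as secondary. Add to section 3.7 that the 18-month contrast is the only confirmatory test at two-sided 5%. A repeated-measures model over all visits would be a reasonable way to estimate the time course, but it is optional and not needed to remove the contradiction.

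The cost is a change of wording, with no added patients, visits or data. The sponsor gives up the option of claiming the primary on an earlier visit. If several visits are truly meant to be primary, a multiplicity procedure and a new sample size would be required instead. With Bonferroni over seven visits and the plan's own assumptions, that is 180/0.9 = 200 per group, or 400 in all against the planned 270.

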In China, Shenling Baizhu Powder is widely used for respiratory diseases. Thus, it is reasonable to hypothesize that Modified Shenling Baizhu Powder is effective for the treatment of COPD. However, few published data show a meaningful effect of Modified Shenling Baizhu Powder on preventing exacerbation and its long-term (18 months) safety profile in participants with COPD of GOLD stage 1 or stage 2. To resolve these issues, we design this randomized, placebo-controlled , double-blind, prospective study protocol.

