### Eligibility criteria

2.8

Inclusion criteria:

1.Age range 40–85 years, male or female2.Grade 1–2 of the COPD diagnostic criteria in GOLD guidelines^[4]^: 20 minutes after inhalation of salbutamol 400, FEV1/FVC <70%, and 50% predicted value ≤FEV1<80% predicted value3.Participants are in the stable stages of COPD and had no respiratory infections or acute exacerbations of COPD within the past 4 weeks4.Participants who meet the diagnostic criteria for common TCM syndromes with lung-spleen qi deficiency syndrome5.Participants volunteer to take part in the study and to provide informed written consent

Exclusion criteria:

1.Patients with chronic lung diseases in which intervention or treatment is required, such as interstitial lung disease, bronchial asthma, active tuberculosis, or bronchiectasis2.Patients with a combination of severe primary diseases, such as cardiovascular and cerebrovascular diseases, liver and kidney diseases, hematopoietic system diseases, endocrine diseases, severe mental disorders, malignant tumors3.Patients have evidence of alcohol or drug abuse, known or suspected allergy to the study drug or some of its components, and currently uses oral corticosteroids regularly4.Women who are breast-feeding, pregnant, or expecting a child5.Patients who have been involved in any other clinical study in the past 6 months6.Patients unable to successfully use a dry powder inhaler or perform pulmonary function measurements

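### Exacerbation interval, duration and severity, read as per-event measures, would be compared between subsets selected after randomisation

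*Protocol article*

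**What the plan says.** Section 3.2 (Outcome measures) places "Frequency, interval, duration, and severity of COPD exacerbations; time to first COPD exacerbation" in the third item of the secondary list, under the lead "Secondary outcomes: at 1, 3, 6, 9, 12, 15, 18 months". It does not say what value a participant without an attack takes for interval, duration or severity.

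Section 3.7 (Statistical analysis) states that "The intention to treat principle will be followed for all data analysis". It assigns t, rank-sum or chi-square tests by type of data, all two-sided at 0.05, and adds: "In the analysis of the full analysis set, the missing data are substituted by the method of sequence mean value". It makes no exception for a value that is undefined because no event occurred.

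The Introduction gives as one motive for the trial that "few published data show a meaningful effect of Modified Shenling Baizhu Powder on preventing exacerbation". Section 2.8 (Eligibility criteria) asks only that participants "had no respiratory infections or acute exacerbations of COPD within the past 4 weeks". No history of attacks is required, so a good number may have none during the study.

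**The concern.** Frequency and time to first exacerbation are defined for everyone: a person without an attack contributes a zero count or a censored time. Duration and severity of an attack need at least one attack, and an interval between attacks needs two.

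If the granule changes who has attacks, which is part of the trial's rationale, the participants who supply these values differ systematically between arms and randomisation no longer protects the comparison. A difference in mean duration could then reflect which attacks were prevented and not any change in how long attacks last.

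Section 3.7 offers no sound way to handle the others. Leaving event-free participants out departs from its own intention-to-treat statement. Counting them as missing would trigger mean substitution and give them an attack duration or severity they never had, when their burden is zero.

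**Working it through.** **Inputs from the document.** The abstract states that "270 eligible participants will be randomly assigned to either the experimental or control group in a 1:1 ratio", so 135 per arm, and that "The course of treatment is 6 months with 12 months of follow-up", so 1.5 years of observation. The document gives no exacerbation rate, severity mix or duration, so it has no figure of its own to reproduce here. Its sample size rests on FEV1 only. All event figures below are assumptions.

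**Step 1. Direction of the shift.** Take 100 control attacks as 70 mild (6 days each) and 30 severe (14 days each). Mean duration = total days / number of attacks.

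| Assumed effect | Mean days per attack | Severe share | Total days against control |
|---|---|---|---|
| None (control) | (70×6 + 30×14)/100 = 8.4 | 30% | 840/840 = 100% |
| Mild halved | (35×6 + 30×14)/65 = 630/65 = 9.7 | 30/65 = 46% | 630/840 = 75% |
| Both halved | (35×6 + 15×14)/50 = 420/50 = 8.4 | 15/50 = 30% | 420/840 = 50% |
| Severe halved | (70×6 + 15×14)/85 = 630/85 = 7.4 | 15/85 = 18% | 630/840 = 75% |

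Rows two and four have the same 25% fall in total days, yet mean duration moves in opposite directions. Per-event duration and severity therefore do not track benefit reliably.

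**Step 2. How many participants have a value.** With Poisson counts of mean m = 1.5 × yearly rate, the number with a duration is 135 × (1 − e^−m) and the number with an interval is 135 × (1 − e^−m(1 + m)).

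| Attacks per year | m | At least one attack | At least two | No attack |
|---|---|---|---|---|
| 0.2 | 0.3 | 35 | 5 | 100 |
| 0.4 | 0.6 | 61 | 16 | 74 |
| 0.8 | 1.2 | 94 | 46 | 41 |

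The last column (135 minus those with an attack) is the number per arm who would be given an invented duration if event-free participants were treated as missing.

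**Step 3. The subsets differ by arm.** At 0.6 control attacks per year with mild attacks halved, the treated rate is 0.65 × 0.6 = 0.39. Participants with at least one attack number 135 × (1 − e^−0.9) = 80 in control and 135 × (1 − e^−0.585) = 60 in the experimental arm.

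**Step 4. Chance of a significant wrong-way result when only mild attacks are prevented.** A simulation used 135 per arm, 1.5 years, 70% mild attacks averaging 7 days and 30% severe averaging 14 days, attack rates varying between participants (gamma frailty, variance 1), control rates of 0.3, 0.6 and 1.0 per year, and 1,500 trials per setting. Expected duration per attack is 0.7×7 + 0.3×14 = 9.1 days in control. It is 7.63/0.79 = 9.66 days with 30% of mild attacks prevented and 6.65/0.65 = 10.23 days with 50% prevented.

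- A t test of mean duration among participants with attacks called the granule significantly worse in 7–9% of trials (30% prevented) and 14–29% (50% prevented), against about 3% with no effect.
- A t test of total exacerbation days in all randomised participants did so in at most 0.5% of trials when mild attacks were prevented.

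The calculations show a possible reversal for duration and severity. For interval they show only how few participants contribute.

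**The case against.** The strongest reply is that the article never defines these measures. Duration could mean total days per participant with zero for none, and severity could include a grade for none. Such definitions are commonly left to a full protocol or analysis plan. Between-group wording in section 3.2 appears only for lung function, and section 3.7 names tests by data type without mentioning exacerbation measures. A person without an attack has not lost a value, so mean substitution need not apply. This stands as a limit on confidence: a reader might infer that the plan definitely compares only participants with attacks, and the text does not say so. It does not remove the point. Listing frequency separately makes the per-event reading the natural one, and the only missing-data rule shown gives no protection.

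A reader might also infer that a helpful granule will look harmful. That needs mainly mild attacks to be prevented, which nothing in the documents leads one to expect. Equal reduction produces no shift, and fewer severe attacks move the measures the right way.

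Finally, a reader might infer that the question of preventing exacerbations is compromised. It is not: frequency and time to first exacerbation answer it and are defined for everyone. The Discussion's list of what the trial will focus on does not include exacerbations. Frequency reported alongside would also show a reader that attacks were fewer.

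**Conclusion.** The point holds conditionally. If interval, duration and severity are per-event measures, a between-group test of them under section 3.7 is not a randomised comparison, and its bias can go either way. Under the assumed 70/30 mix with 6 and 14 days, mean duration per attack is 9.7, 8.4 or 7.4 days when mild attacks, both types or severe attacks are halved, against 8.4 in control. The treatment is beneficial in all three cases. Interval has the thinnest base: about 5 to 46 of 135 per arm at 0.2 to 0.8 attacks per year. These sizes rest on assumed rates, mix and durations; the selection itself does not.

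The FEV1 primary outcome, exacerbation frequency and time to first exacerbation are untouched. Severity is moderate to low, since only secondary outcomes are involved. Confidence is moderate, because a plan not shown may already define these outcomes for every participant.

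**What to change.** In section 3.2 and the analysis plan, define the measures for between-group comparison in all randomised participants: total exacerbation days per person-year and the rate of severe exacerbations, alongside the frequency already listed. State that a participant without an attack counts as zero over the time observed, and is not missing and not subject to mean substitution. Report per-event duration, severity and interval descriptively among participants with attacks, with the number contributing in each arm and no P value. If a fuller plan already does this, one clarifying sentence in the outcome section is enough.

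The cost is wording only. The same exacerbation records serve, with no added participants or visits. The downside is that three per-event comparisons lose their significance test.
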